**Health economics and cost-effectiveness**

Using established models describing the progressive stages of chronic HCV, we will aim to translate the outcomes of the trial into an estimated number of disability-adjusted life years (DALYs) averted. This will follow the approach used within the 2010 global burden of disease study. In addition, we will aim to administer the EQ5D-3L quality of life questionnaire to all of the enrolled patients at baseline (before treatment), midway during treatment, and after treatment (at the EOT+12 week visit). This data will allow us to measure the number of quality-adjusted life-years (QALY) saved due to the therapy.

**Pharmacokinetics**

Venous plasma samples will be collected for sofosbuvir, and its main metabolite GS-331007, as well as daclatasvir for pharmacokinetic evaluations. Dense pharmacokinetic samples will be collected in 40 patients with mild liver disease. Five samples will be collected in each patient after the first dose and at day 28, resulting in a total of 10 samples per patient. Sparse pharmacokinetic samples will be collected in all patients. A total of three samples per patient will be collected randomly at D7, D14 and the last day of treatment (either D28 or D56). The pharmacokinetic properties of these drugs will be evaluated with respect to viral dynamics in order to characterise the pharmacokinetic-pharmacodynamic properties of sofosbuvir and daclatasvir.

**Blood sampling and laboratory analysis**

Blood samples to monitor safety and response to therapy will be drawn from each subject according to trial assessment schedule. Samples for hematological and biochemical tests will be sent to HTD clinical laboratory (ISO 15189;2012). Any critical values identified in hematology or biochemistry paprameters will immediately be reported to the study physician. HCV viral load will be determined by Cobas TAqMan HCV test v2.0 (Roche Molecular diasgnostic) (LOD 15IU/ml) throughout the study. HCV genotype will be determined by NS5B, Core, 5’ UTR sequencing.

Additional blood samples for research purposes, as detailed in the trial assessment schedule, will be collected, stored, and anonymised. These samples will include plasma, serum, DNA, RNA and whole blood. Samples will be collected according to standard local procedures. Samples for virological, genetics and immunological assays will be processed and stored at -80C or in liquid nitrogen at OUCRU laboratory. Chain of custody of all samples will be maintained during the study period and therafter as approved by the EC. IL28B and other SNPs will be determined by chip tecnology available at Oxford University. Full length viral sequencing will be done to study variation in the viral genome associated with treatment come. Host genetic analysis including SNP in IL28B gene and other known SNPs will be studied and their association with treatment outcome will be analyzed. Samples will be analyzed for biomarkers for HCV infections, liver disease and their association with clinical outcome, in particular the cytokines IL-10, IL-6 and TNF[[20](#_ENREF_20)] and IP-10 [[21](#_ENREF_21)]. All testing will be done by trained technicians following GCLP standard. All samples will be stored at OUCRU and will be shared with investigators in Oxford University for analysis as necessary. Blood samples may be shipped for experimental work to laboratories outside Vietnam (to Oxford University and Imperial College who are investigators in this study).

All data arising from this collaborative project will remain the shared property of HTD, collaborators, and OUCRU. Use of these samples and data beyond the stated objectives of this study will require the joint agreement of all the Investigators. Additional investigations will only be performed with the approval of the appropriate ethical committees and the endorsement of the responsible investigators.

- 1. Early Stopping of Follow-up

If a participant chooses to discontinue their trial treatment, they should always be invited and encouraged to continue follow-up “off study drug, on study”. If they do not wish to remain on trial follow-up, however, their decision must be respected and the patient will be withdrawn from the trial. However, in this situation, the participant should be asked whether or not they are willing to provide follow-up through their routine records (that is, not to attend study-specific visits but to allow data collected within the clinic to be used for trial comparisons). The OUCRU CTU should be informed of the participant’s decision regarding withdrawal (no further data of any kind, or follow-up through routine records) in writing using the appropriate CRF. Prior to withdrawing from the trial, the participant will be asked to have assessments performed as appropriate for the final EOT+12 week visit although they would be at liberty to refuse any or all individual components of the assessment.

If a participant withdraws from the trial, the medical data collected during their previous consented participation in the trial will be kept and used in analysis. Consent for future use of stored samples already collected can be withdrawn when leaving the trial early (but this should be discouraged and should follow a discussion). If consent for future use of stored samples already collected is withdrawn, then all such samples will be destroyed following the policies of the institution where the samples reside at the time.

Participants may change their minds about stopping trial follow-up at any time and re-consent to participation in the trial, including taking repeat samples.

Participants who stop trial follow-up early will not be replaced, as the total sample size includes adjustment for losses to follow-up.

Consent will be sought for long-term follow-up through routine records in order to ascertain long-term impact of treatment on morbidity and mortality including cirrhosis and hepatocellular carcinoma.

- 1. Loss to Follow-up

In the statistical analysis, a participant will be classified as ‘lost to follow-up’ if they have not been seen at the final EOT+12 week visit within a [-6,+6] week window.

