| Trial Title | A pilot study to assess shortened therapy for hepatitis C infected adults in Vietnam |
| ACRONYM | **SEARCH-1** |
| Trial Design | The study is a single arm, open label trial evaluating strategies for shortening treatment for individuals infected with hepatitis C virus (HCV) based on their early response to directly acting antiviral (DAA) therapy. Participants will be stratified by stage of liver fibrosis to one of two strategies based on virological response at either 48 hours (mild disease) or 14 days (cirrhosis) of treatment. |
| Trial Population/Participants | 103 adults (≥ 18 years) chronically infected with HCV genotypes 1 and 6 |
| Setting | Hospital for Tropical Diseases, Ho Chi Minh City, Vietnam |
| Intervention | Response-guided short course treatment of HCV with sofosbuvir and daclatasvir |
| Study Hypothesis | Shortened HCV treatment courses based on early viral responses to sofosbuvir and daclatasvir therapy will achieve high rates of cure |
| Primary Outcome Measure | Sustained Virological Response (SVR) defined as plasma HCV RNA persistently <LLOQ (lower limit of quantification) through 12 weeks after the end of first treatment without prior failure (see section 2.2) |
| Secondary Outcome Measures | - SVR12 after the end of the combined first and any re-treatment phases (mild patients only) - lack of initial virological response - serious adverse events - grade 3/4 clinical adverse events - adverse events of any grade leading to change in treatment (SOF, DCV or any other medication) - adverse reactions (any grade) (considered definitely/probably/possibly related to SOF or DCV) |
| Participant follow-up | 12 weeks from completion of last therapy |
| Study Duration | 2 years |
| Ancillary Studies | Pharmacokinetics of Sofsobuvir/Daclatasvir  Health economic analysis of HCV treatment |

Trial Schema

[figure not shown]

TRIAL ASSESSMENT SCHEDULE

See Appendix II, Trial Assessment Schedule

Abbreviations

| Abbreviation | Expansion |
| --- | --- |
| AE | Adverse event |
| AR | Adverse reaction |
| ART | Antiretroviral therapy |
| ARV | Antiretroviral |
| bid | Bis in die (twice a day) |
| BNF | British National Formulary |
| CF | Consent Form |
| CI | Chief Investigator |
| CI | Confidence interval |
| COM | Clinical Operations Manager |
| CPA, CPB, CPC | Child’s Pugh (classification) A, B, C |
| CPM | Clinical Project Manager |
| CRF | Case Report Form |
| CTU | Clinical Trials Unit |
| DAA | Direct Acting Antiviral |

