**Risks and benefits at patient and societal level**

The primary benefit of participation for individual patients in this trial is that >90% of individuals will achieve cure of hepatitis C without interferon-based treatment within the protocol. For many, interferon will have been a barrier to accessing and/or adhering to treatment previously. Barriers to accessing treatment are likely to remain even with increasing availability of directly acting antivirals (DAAs), as demand for treatment is expected to exceed the capacity to deliver it in setting such as Vietnam. The primary outcome measure (sustained virological response 12 weeks after end of treatment, SVR12) has been associated with significant reductions in all-cause mortality, cirrhosis and liver cancer [[18](#_ENREF_18)], and so achieving cure will significantly reduce individual patient’s future risks of these events. The study will use licensed medications that have been recommended as part of the WHO Essential Medicines list since 2015.

1. trial design and endpoints
   1. Description of trial design

The study is a single arm, open label trial with the objective of identifying successful strategies for shortening treatment for individuals chronically infected with hepatitis C based on their early response to therapy.

It will test the hypothesis that early responses to treatment with sofosbuvir and daclatasvir will identify a group of individuals able to achieve high cure rates with shortened courses of treatment. Participants will be stratified by stage of liver disease to one of two strategies based on virological response after either 48 hours (non-cirrhotic) or 14 days (cirrhosis) of starting treatment.

- 1. trial endpoints

Primary endpoint

The primary endpoint for the trial is Sustained Virological Response (SVR12) defined as plasma HCV RNA <LLOQ (lower limit of quantification, <15 IU/ml) 12 weeks after the end of first treatment without prior failure defined as either:

i. two consecutive measurements of HCV RNA >LLOQ (taken at least one week apart) after two consecutive visits with HCV RNA <LLOQ, at any time, with the latter confirmatory measurement also being >2000 IU/ml

ii. two consecutive measurements of HCV RNA (taken at least one week apart) that are >1 log10 increase above HCV RNA nadir on treatment and >2000 IU/ml, at any time.

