Cure is defined using the LLOQ, <15 IU/ml, 12 weeks after end of treatment (EOT). However, failure before this timepoint is defined using a slightly higher threshold because patients have been observed to achieve cure despite having low-level viraemia at the EOT or shortly after, and so they do not need re-treatment to achieve cure. In practice any patient with low-level viraemia <2000 IU/ml either cures or viral load rises above this level. This will be carefully reviewed by the Data Monitoring Committee. This is the same definition as used in the UK STOP-HCV-1 trial ISRCTN 37915093), where the Data Monitoring Committee has similarly reviewed individual patient viral load trajectories and has not raised any concerns.

Secondary endpoints

Secondary endpoints for the trial are

- SVR12 after the end of the combined first and any re-treatment phases (mild patients only)
- lack of initial virological response (<1 log_10_ decrease in HCV viral load from baseline)
- serious adverse events
- grade 3/4 clinical adverse events
- adverse events of any grade leading to change in treatment (SOF, DCV or any other medication)
- adverse reactions (any grade) (considered definitely/probably/possibly related to SOF or DCV)

1. Participant identification

There will be no exceptions to eligibility requirements at the time of recruitment. Questions about eligibility criteria should be addressed prior to attempting to enrol the patient – clarifications may be sought from the trial team.

The eligibility criteria are the standards used to ensure that only medically appropriate participants are considered for this study. Participants not meeting the criteria should not join the study. For the safety of the participants, as well as to ensure that the results of this study can be useful for making treatment decisions regarding other participants with similar diseases, it is important that no exceptions be made to these criteria for admission to the study.

Participants will be considered eligible for enrolment in this trial if they fulfil all the inclusion criteria and none of the exclusion criteria as defined below.

Recruitment will take place from clinics within the Hospital for Tropical Diseases in Ho Chi Minh City.

- 1. Inclusion Criteria

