All participants will be followed by the site clinic teams for 12 weeks after the end of first-line treatment or re-treatment (where relevant) for evaluation of virological response and toxicity. Outcome measures will be assessed at clinic visits (see Trial Assessment Schedule). For the mild disease cohort, the first DAA dose should be taken in the clinic and the blood draws on day 1 and day 2 should be taken within ±3 hours of 24 and 48 hours post this first dose wherever possible. Other on treatment visits should occur within ±1 days wherever possible, and the post end-of-treatment (EOT) visits within ±3 days. However, if this is not possible, a visit (with all the appropriate tests and evaluations) should still take place outside this window to ensure that trial outcomes are ascertained as accurately as possible in real-time.

All those recording clinical data will be identified and receive appropriate training and sign the Delegation Log. Clinical data will be obtained through consultation with the participant, their medical team, or their medical records. Laboratory measures and resource utilisation will be extracted from participant notes/electronic records; study nurses will administer quality of life questionnaires to participants.

Any additional visits or diagnostic/laboratory tests needed for patient management should occur as required at the discretion of the treating physician. Results from these investigations should be recorded on CRFs, but only the investigations specified in the Trial Assessment schedule are required in all participants.

- 1. Procedures for Assessing Efficacy

The primary means of assessing efficacy is the HCV viral load. HCV viral load will be assayed locally in line with existing clincial practice. This will also enable swift detection of virological failure and move to re-treatment for participants in the mild disease cohort.

HCV viral resistance will be measured within the SEARCH consortium retrospectively in batches during the trial. This will be done using next-generation sequencing approaches. Viral genotype will also be characterised using these assays enabling an assessment of whether treatment failure is a genuine recurrence (same genotype, closely genetically related) or a new infection (different genotype, or same genotype but genetically too distant to be compatible with within-host evolution). Summary resistance data will be shared with the local research team.

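### The analysis window in Section 6.6 opens six weeks after treatment, so on the natural reading an early negative sample can stand in for the 12-week cure result

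*Protocol*

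**What the plan says.** Four parts of the protocol bear on which sample decides the primary endpoint.

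- **Section 2.2 (endpoint).** SVR12 is "plasma HCV RNA <LLOQ (lower limit of quantification, <15 IU/ml) 12 weeks after the end of first treatment without prior failure". Failure before that point requires two consecutive raised values, and under the first criterion this is qualified by "with the latter confirmatory measurement also being >2000 IU/ml". The tolerance is deliberate, because "patients have been observed to achieve cure despite having low-level viraemia at the EOT or shortly after".
- **Section 6.1 (visit timing).** The target is "the post end-of-treatment (EOT) visits within ±3 days", wherever possible. If that cannot be met, "a visit (with all the appropriate tests and evaluations) should still take place outside this window".
- **Sections 6.5 and 6.6 (withdrawal and loss).** A participant who is withdrawing is asked to have the assessments of the final visit first. In the analysis, a participant is lost to follow-up "if they have not been seen at the final EOT+12 week visit within a [-6,+6] week window".
- **Section 9.2 (analysis).** SVR12 is analysed as observed. Week-12 values missing through a failed assay or a missed visit are multiply imputed within stratum, using all viral loads and baseline characteristics.

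Separately, the Summary of Trial gives the primary outcome as "plasma HCV RNA persistently <LLOQ (lower limit of quantification) through 12 weeks after the end of first treatment without prior failure (see section 2.2", with that cross-reference attached. The abbreviation list glosses SVR in the same persistent sense.

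**The concern.** The trial asks whether shortened treatment leads to relapse. A sample taken soon after treatment gives less time for relapse to appear than one at 12 weeks. If the analysis accepts a negative from week 6 onward as the final result, a participant who relapses between that sample and week 12 is counted as cured. The planned imputation, which would carry the uncertainty, is not triggered because the participant counts as seen.

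The success criterion in Section 9.1 is a lower 95% confidence limit above 70%, on about 37 participants per stratum. With so few, single classifications matter.

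A smaller matter is that the Summary and Section 2.2 can give different answers for the same person.

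**Working it through.** **1. Reproducing the plan's own figure.** Section 9.1 gives a target of 90%, an unacceptable rate of 70%, one-sided alpha 0.05 and power 90%. The smallest n for an exact single-arm binomial test is 37, with success at 31 or more: P(X ≥ 31 | 37, 0.70) = 0.0440 and P(X ≥ 31 | 37, 0.90) = 0.9289. Totals are 37/0.65/0.95 = 59.9 (stated 60) and 37/0.90/0.95 = 43.3 (stated 43). The stated sizes reproduce, and nothing below changes them.

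**2. The window.** 12 − 6 = week 6 and 12 + 6 = week 18 after treatment. Six weeks is 42 days, against a visit tolerance of 3 days.

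**3. Tracing one participant.** Suppose a participant withdraws at week 7 after treatment and has the final-visit assessments that Section 6.5 requests, with HCV RNA below LLOQ.
- Section 6.6: seen inside weeks 6 to 18, so not lost.
- Section 9.2: the assay worked and the visit took place, so on the natural reading there is nothing to impute, and the result is analysed as observed.
- Section 2.2: the endpoint is at 12 weeks, for which no sample exists.

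No section says which of these prevails.

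**4. What one reclassified participant does.** The exact (Clopper-Pearson) lower limit for x successes in n is the a-quantile of Beta(x, n − x + 1), with a = 0.05 one-sided and 0.025 for a two-sided 95% interval.

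| x/37 | Proportion | One-sided lower | Two-sided lower |
|---|---|---|---|
| 30 | 81.1% | 67.4% | 64.8% |
| 31 | 83.8% | 70.5% | 68.0% |
| 32 | 86.5% | 73.7% | 71.2% |

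The 70% line falls between 30 and 31 one-sided, and between 31 and 32 two-sided. Each participant moves the proportion by 1/37 = 2.7 points. Section 9.2 plans Poisson-regression intervals, so the exact limits are illustrative.

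**5. Expected bias.** The documents give no rates, so these are assumptions. Let w be the share of participants scored on an early sample only (unrelated to cure status), f the share of non-cures still below LLOQ at that sample, and p the true cure rate. The observed rate is p + (1 − p)·w·f.

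- At p = 0.90 the bias is 0.1·w·f. For w = 5%, f = 30%: 0.1 × 0.05 × 0.30 = 0.0015, or 0.15 points. For w = 100%, f = 30%: 3 points.
- At p = 0.70 the observed rate is 0.70 + 0.30·w·f, and the type I error is P(X ≥ 31 | 37, observed rate):

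| w | f = 5% | f = 30% |
|---|---|---|
| 5% | 0.045 | 0.050 |
| 25% | 0.049 | 0.078 |
| 100% | 0.065 | 0.315 |

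The reference value is 0.044. The last row is a bound, not an expectation.

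**6. The two endpoint wordings.** Take an illustrative participant with a single value of 100 IU/ml shortly after treatment and below 15 IU/ml at week 12. Under Section 2.2 there is no failure, since 2000 IU/ml is not exceeded, so SVR12 is achieved. Under the Summary, RNA was not "plasma HCV RNA persistently <LLOQ (lower limit of quantification) through 12 weeks after the end of first treatment without prior failure", so it is not achieved. Twice-weekly viral loads for four weeks after treatment in Stratum A (Section 5.1) give many chances to see such a value.

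**The case against.** Section 6.6 is written as a rule on loss to follow-up and does not expressly say which HCV RNA result scores SVR12. Section 2.2 fixes the endpoint at 12 weeks. It can be argued that a participant seen at week 7 and not again has missed the week-12 visit and is imputed under Section 9.2. The ±3 days is a scheduling target, so it does not contradict an analysis window, and detailed sampling windows commonly belong in the SAP, which is not shown. Stratum A's twice-weekly sampling catches early rebound, and the schedule tables of Appendix II are not available, so planned sampling between weeks 6 and 12 cannot be checked.

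Much of this stands. That early samples are scored is an inference, and it must be put as one. It does not dispose of the point, because Section 6.6 is stated for the statistical analysis and counts a week-7 attendance as the final visit, and Section 6.5 supplies a route by which that attendance carries the final assessments. This is a rule the protocol states, not a detail left open. The intensive sampling stops four weeks after treatment, before the window opens.

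A reader might infer more than the documents support:
- **Three rival scoring rules.** There are two wordings of the endpoint and a visit window not linked to either. The Summary refers to Section 2.2, so the governing text is identifiable.
- **An error in one direction only.** Section 2.2 notes that low-level viraemia near the end of treatment can clear, so an early positive could also be scored wrongly as non-cure.
- **A likely shift of two participants, equal to the planned 5% loss.** The 37 is already net of that loss (60 × 0.65 × 0.95 = 37.1; 43 × 0.90 × 0.95 = 36.8). With 6 non-cures in 37, two participants picked at random would both be non-cures with probability (6/37)(5/36) = 2.3%.

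**Conclusion.** The point holds in a limited form. The Section 6.6 window and the Section 9.2 imputation rule together lead, on the natural reading, to a negative sample from as early as week 6 being scored as the 12-week outcome. This conflicts with the timing in Section 2.2 and can miss later relapse, biasing cure mainly upward.

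The documents do not give the size. Under the stated assumptions it is negligible if about 5% are sampled early and becomes material only if early sampling is common. What justifies a change is the narrow margin: close to 70%, one participant of 37 decides the conclusion under either interval convention. The change is also nearly free. The difference between the Summary and Section 2.2 is real but a minor matter of alignment.

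**What to change.** In Section 6.6, separate loss to follow-up from endpoint scoring and link the latter to Sections 2.2 and 9.2:

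1. A result below LLOQ counts as SVR12 only if sampled at about 12 weeks after the end of first treatment. Tie the lower bound to the visit tolerance in Section 6.1; the upper bound may stay at +6 weeks.
2. Participants whose only negative samples are earlier are treated as missing at week 12 and imputed under Section 9.2, with their earlier viral loads as predictors.
3. A confirmed failure before that time, as defined in Section 2.2, remains a failure.

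In the Summary, replace the persistent wording with the Section 2.2 definition it already refers to, and adjust the SVR entry in the abbreviation list to match.

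The cost is wording, plus a few more participants imputed instead of scored as observed. The sample sizes of 37, 60 and 43 do not change.
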